**Fig. 2 f0010:**
[figure not shown]
Excerpts from the *marena* intervention.

#### GSA-Online plus

2.4.2

*GSA-Online plus* is an internet-based psychotherapeutically oriented aftercare intervention (Beutel et al., 2018) which aims to support occupationally stressed rehabilitants during return to work. The efficacy and feasibility of the therapeutic writing intervention has already been demonstrated in an RCT (Zwerenz et al., 2017) and an implementation study (Zwerenz et al., 2019).

While still in inpatient rehabilitation, participants can access explanatory and motivational videos to familiarize themselves with the program and select a specific day of the week to receive writing prompts. Following discharge, participants receive weekly writing prompts over a period of 12 weeks. The participants respond with a diary entry and are instructed to articulate and identify interpersonal and intrapsychic problems at the workplace. The online therapists reply to the diary entries by providing encouragement and support to deal with individual job-related problems, focusing on stabilizing work capacity.

The first writing prompt is standardized. The following prompts and feedback are personalized, depending on past diary entries. Diary entries are accessible only to the individual participant and the study team. Communication takes place only within the intervention. Participants receive e-mail reminders on new, due, and overdue writing prompts as well as when feedback from the online therapist is available.

### Control condition

2.5

Participants in the CG will have limited access to *marena* with questionnaires and voluntary weekly surveys. We chose to use an optimized control condition in anticipation of higher participation during recruitment at the rehabilitation centers and higher response rates to follow-up assessments. Participants in both intervention arms will have unrestricted access to usual treatment options.

### Outcome measures

2.6

Outcomes are assessed at the end of rehabilitation (T0) as well as three (T1), six (T2), nine (T3), and 12 months after discharge (T4). Table 2 provides an overview of the data collected at the five measuring points. We carefully selected compact instruments to reduce the burden on the participants.

**Table 2 t0010:** Schedule of assessments.

Construct	Questionnaire	T0	T1	T2	T3	T4
Primary Outcome						
Work status	employment status at 6 and 12 months of follow-up	x	x	x	x	x

Secondary Outcomes						
Successful completion of a graded return to work	Self-constructed items	x	x	x	x	x
Successful application for benefits for participation in working life	Self-constructed items	x	x	x	x	x
Current work ability	WAS^a^	x	x	x	x	x
Social-medical risk index	SIBAR^a^	x	x	x	x	x
Health related quality of life	EQ-5D^a^	x	x	x	x	x
Social Support	OSSS-3	x	x	x	x	x
Coping	BRCS	x	x	x	x	x
Anxiety	GAD-7	x	x	x	x	x
Depression	PHQ-9	x	x	x	x	x
Psychosocial Stress	PHQ-Stress	x	x	x	x	x
Somatic symptoms	SSS-8	x	x	x	x	x
Subjective prognosis of gainful employment	SPE	x	x	x	x	x
Satisfaction with *marena*	ZUF-8 *marena*^b^, ^d^			x		
Usability of *marena*	UEQ *marena*^b^, ^d^			x		
Helpfulness of *marena*	Self-constructed items^b^, ^d^			x		
Satisfaction with *GSA-Online plus*	ZUF-8 *GSA-Online plus*^c^, ^d^		x			
Usability of *GSA-Online plus*	UEQ *GSA-Online plus*^c^, ^d^		x			
Helpfulness of *GSA-Online plus*	Self-constructed items^c^, ^d^		x			

Other measures						
Demographics	Socio-Demographic Data	x				
Treatment data	Clinical Routine Data	x				
Occupational data	Clinical Routine Data	x				
Recommendations for rehabilitation aftercare	Clinical Routine Data	x				
General Feedback	Self-constructed items^b^		x	x		x
Adherence *marena*	Number of sessions in the intervention^b^, ^d^ Number of completed tasks^b^, ^d^ Number of completed weekly survey^b^, ^d^ Number of media playback^b^, ^d^ Number of visits to the intervention areas and individual pages^b^, ^d^	n. a.	n. a.	n. a.	n. a.	n. a.
Adherence *GSA-Online plus*	Number of completed writing-impulses^c^, ^d^	n. a.	n. a.	n. a.	n. a.	n. a.

a Work ability status, health condition and occupational stress are additionally provided in a weekly survey, so they are regularly answered during the intervention phase.

b Only participants of IG subgroup 1.

c Only participants of IG subgroup 2.

d Objective data collected within the programs.

#### Primary outcome

2.6.1

The primary outcome will be work status at six (T2) and 12 (T4) months follow-up assessment. Work status at 6 months will be considered as primary endpoint and is defined as positive if the participant is working (no unemployment, no reduced earning capacity pension) and reports a maximum of six weeks of sick leave not related to graded return to work. Work status at 12 months is defined as positive if the participant is working and reports maximum 12 weeks of sick leave not related to graded return to work. These cut-offs were chosen in line with previous analyses of return to work in German rehabilitation (Mau et al., 2002; Bethge et al., 2011). We do not include sick leave during a graded return to work measure, as participants are formally on sick leave, receiving financial support from their healthcare provider, but are back at their workplace.

#### Secondary outcomes

2.6.2

Successful completion of a graded return to work is assessed with self-constructed items about the planning, execution, completion, discontinuation, and early termination of the measure.

Successful application for benefits for participation in working life is assessed with self-constructed items about the planning, execution, and completion of an application, as well as the (partial) approval or rejection of benefits.

Current work ability is assessed with the Work Ability Score (WAS), the first single-item question in the well-established Work Ability Index (WAI; Hasselhorn and Freude, 2007). Participants rate their current work ability compared with their lifetime best. The scale ranges from 0 to 10.

Social-medical risk index is assessed with the short and validated ‘Screening Instrument for the Assessment of Need for Occupational Related Treatment in Medical Rehabilitation’ (SIBAR; Bürger and Deck, 2009) which comprises three subscales: (1) the social-medical index (risk of early retirement); (2) occupational stress, and (3) the subjective need for occupation-related treatment. We will assess scale 1 and scale 2. The social-medical index ranges from 0 to 19. A need for occupational treatment is indicated if the score is 8 or higher. The single global rating on occupational stress of subscale 2 is: ‘Overall, my professional situation is… very stressful… to … very fulfilling’ measured on a five-point Likert scale from 0 to 4. The retest-reliability of the different subscales ranges from rep = 0.37 to rep = 0.96 in a previous study by Bürger and Deck (2009).

Subjective prognosis of gainful employment is assessed by a 3-item scale measuring the subjective prognosis of future work capacity and employment status (SPE scale; Mittag and Raspe, 2003).

Health related quality of life is assessed through the European Quality of Life Questionnaire (5 Dimensions; EQ-5D; Ludwig et al., 2018). The instrument includes a vertical EQ Visual Analogue Scale (EQ-VAS), which provides a single global rating of self-perceived health. The scale is measured on a Likert scale from 0 to 10 (0 = ‘worst imaginable health’ to 100 = ‘best imaginable health’).

Somatic symptoms are assessed with the symptom scale-8 (SSS-8; Gierk et al., 2014). The 8 item scale assess different symptoms on a Likert-scale ranging from 0 = ‘not at all‘ to 4 = ‘very much’. An example item is ‘During the past 7 days, how much have you been bothered by back pain?’.

Coping is assessed by the Brief Resilient Coping Scale (BRCS). An example out of the four items is: ‘Regardless of what happens to me, I believe I can control my reaction to it’. The Likert-scale ranges from 1 = ‘does not describe me at all’ to 5 = ‘describes me very well’.

Psychosocial Stress is assessed with the subscale ‘PHQ-stress’ from the Patient Health Questionnaire (PHQ-D; Löwe et al., 2002). An example item is: ‘How much did you feel impaired by stress at work or school in the last 4 weeks?’. The 10 items include health, work/financial, social, and traumatic stress and the ratings comprise 0 = ‘not at all bothered’, 1 = ‘bothered a little’, and 2 = ‘bothered a lot’.

Depression is assessed with the Depression Module (PHQ-9) of the PHQ-D (Spitzer et al., 1999). An example item of this scale is: ‘Over the last two weeks, how often have you been bothered by feeling tired or having little energy?’. The response format is a 4-point Likert-scale ranging from 0 = ‘not at all’ to 3 = ‘nearly every day’.

Anxiety is assessed with the Generalized Anxiety Disorder Scale-7 (GAD-7; Spitzer et al., 2006). An example item is: ‘Over the last two weeks, how often have you been bothered by not being able to stop or control worrying?’. The response format ranges from 0 = ‘not at all’ to 3 = ‘nearly every day’ and corresponds to a 4-point Likert-scale.

Social Support is measured by the Oslo Social Support Scale (OSSS-3; Dalgard and Brevik, 1996). A total of three items assess the level of perceived social support. The response format varies from item to item. Both 4-point and 5-point Likert-scales are used. Higher values indicate greater social support. An example item is: ‘How much interest and concern do people show in what you do?’.

Satisfaction with treatment is assessed with a modified version (wording adapted for the online-interventions) of the Client Satisfaction Questionnaire (CSQ-8; Attkisson and Zwick, 1982). To adapt the questionnaire for our sample, the German version called ZUF-8 by Schmidt et al. (1989) will be used. The Likert-scale ranges from 1 to 4, with higher values indicating higher satisfaction. An example item is: ‘Overall, how satisfied are you with the treatment you have received?’.

User Experience is assessed using the 8-item User Experience Questionnaire (UEQ; Schrepp et al., 2017). The Likert-scale ranges from 0 to 6 with two poles each, for example, 0 = ‘confusing’ and 6 = ‘clear’.

Helpfulness is assessed with quantitative and qualitative self-constructed items. Participants will rate overall helpfulness on a 5-point Likert-scale ranging from 1 = ‘very much’ to 4 = ‘not at all’. Furthermore, participants are asked to indicate which elements of the interventions were particularly helpful/not helpful.

#### Other assessments

2.6.3

Demographic and socioeconomic characteristics from clinical routine data include age, sex, marital status, level of education, professional qualifications and apprenticeships or studies.

Occupational data include weekly working hours, receipt or application for a pension, unemployment at the time of admission, and incapacity to work in the last 12 months before admission to rehabilitation.

Inpatient treatment data includes admission and discharge dates, discharge type, and ICD 10 diagnoses.

Recommendations for medical procedures and rehabilitation aftercare by the rehabilitation clinic are documented.

General feedback is assessed through a self-constructed item (‘What else would you like to tell us?’).

Adherence is assessed in different areas throughout *marena*. To analyze the use of the task organizer the number of completed tasks will be examined in relation to the number of tasks that became active in the participant's aftercare plan. Adherence is operationalized by the percentage of participants who completed at least the lower quartile of the provided tasks (in relation to the sample). Additionally, the number of sessions, completed weekly surveys, media playback, visits to the intervention areas, and individual pages will be analyzed. To operationalize adherence to *GSA-Online plus*, the number of completed writing-impulses will be assessed. Adherence will be operationalized by the percentage of participants who wrote at least the lower quartile of diary entries written in the sample.

### Sample size

2.7

The sample size was determined a priori using SAS 9.4 software. A Power analysis based on a power of 0.80, two-sided testing, an alpha-rate of 5 %, and a randomization ratio of 3:1 was conducted. According to Bethge (2017), Odds Ratios of 3.49 (referring to Streibelt and Bethge, 2014) and 2.41 (in Bethge et al., 2011; overall in Streibelt and Bethge, 2014) were observed for work-related occupational rehabilitation programs versus medical rehabilitation with regard to work status 6 months after discharge from rehabilitation. We plan more conservative with an Odds Ratio of 2.0. According to Bethge (2011), a work status rate of 51 % in the CG could be assumed. These assumptions resulted in a total sample size of *N* = 360 required for 80 % power and a binary logistic regression model to analyze the primary endpoint. When considering a correlation of ρ = 0.4 with indicators of specific occupational problems (at least 3-months of incapacity to work before rehabilitation, unemployment at the time of application, and the socio-medical assessment of limited performance in the last occupational activity; see also Bethge, 2017), the sample size can be reduced by ρ2 = 16 % to *N* = 320, due to the reduction of total variance through the explained variance of the covariates. Based on an estimated dropout rate of 20 % at the follow-up assessments T1 (at the end of the *GSA-Online plus* intervention) and T2 (at the end of the *marena* intervention) we plan to randomize *N* = 400 patients.

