### Recruitment and eligibility criteria

2.2

A total of *N* = 400 rehabilitants are planned to be included in the study. Participants with various indications will be recruited during inpatient psychosomatic, orthopedic, or cardiological treatment in four rehabilitation centers in Germany. Rehabilitation entails an intensive examination, information about the individual's disease or disability, and the definition of rehabilitation goals to be achieved through various on-site measures. Patients are taught coping strategies to help them cope with the illness or disability in everyday life after rehabilitation. Since the majority of patients in rehabilitation are currently unable to work or are at risk of reduced earning capacity, this also entails dealing with occupational problems. Medical rehabilitation typically lasts 3 weeks. Psychosomatic rehabilitation typically last five or six weeks.

All rehabilitants are screened for eligibility based on clinical routine data through the clinic staff of the rehabilitation centers. The inclusion criteria are: (1) planned return to work (full- or part-time); (2) age 18 to 65 years; (3) (undisturbed) access to a computer/mobile device and the internet; and (4) German Pension (federal or regional) or statutory health insurance as rehabilitation institution. The exclusion criteria are (1) current unemployment or reduced earning capacity pension with no immediate prospect of employment and (2) negative prognosis for employment (ability to work on the general labor market <3 h as assessed in rehabilitation). No specific diagnoses will be excluded from participation.

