### Statistical analysis for primary and secondary outcomes

2.9

All data analyses will be performed after completion of data collection and on intention-to-treat basis. The significance level for all analyses will be defined as *p* = .05. If appropriate, results will be displayed by adjusted estimates from the analysis model, and their respective 95 % confidence intervals. Descriptive statistics will be used to describe demographics and baseline characteristics. To examine differences between IG and CG in the dichotomous primary outcome work status at 6 months (T2, primary endpoint) and 12 months (T4, secondary endpoint), a binary logistic regression model with fixed and random effects will be performed. In the logistic regression model the following parameters will be considered as fixed effects: treatment group (IG/CG), study site, operating system (android/iOS), at least 3-month incapacity for work before rehabilitation (yes/no), and unemployment at the time of admission to rehabilitation (yes/no). The social-medical risk index (SIBAR) as a continuous parameter will serve as a random effect. In addition, per protocol analyses will be performed to examine the impact of dropouts on study results. Dichotomous secondary outcomes will be analyzed accordingly. Continuous outcome measures will be analyzed with a covariance model for repeated measures. Compound symmetry will be assumed. Additionally, per protocol analyses (based on data of those participants who completed at least the lower quartile of tasks provided in *marena* in relation to the sample and participants who wrote at least the lower quartile of diary entries written in the *GSA-Online plus* sample) will be performed to examine the impact of dropouts on study results. Furthermore, other possible influencing factors (e.g., IG subgroup 1 and IG subgroup 2, received aftercare vs. not received aftercare) will be examined in an exploratory way. The results will also be displayed by rehabilitation center to explore whether obvious differences in effect sizes by rehabilitation center are apparent.

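### A 16% reduction of N = 360 gives about 303, not 320, and the 80% power claim depends on covariates that sections 2.7 and 2.9 list differently

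*Protocol article*

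**What the plan says.** Protocol article, section 2.7 (Sample size), sets these inputs: "A Power analysis based on a power of 0.80, two-sided testing", a 5% alpha, and "a randomization ratio of 3:1 was conducted". The effect size is set below the published values: "We plan more conservative with an Odds Ratio of 2.0". The control-group rate of positive work status is taken as 51%. The result is a total of 360.

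The section then assumes a correlation of 0.4 with indicators of occupational problems and says that the total can fall by 16% to "320, due to the reduction of total variance through the explained variance of the covariates". Three indicators are named:

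- three or more months of incapacity before rehabilitation;
- unemployment, dated at application;
- "the socio-medical assessment of limited performance in the last occupational activity".

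Allowing for 20% dropout, the plan randomises 400.

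Section 2.9 lists the fixed effects of the primary logistic model: treatment group, site, operating system, the incapacity indicator, and "unemployment at the time of admission to rehabilitation (yes/no"). The social-medical risk index (SIBAR) enters as a random effect. The limited-performance assessment is not listed. In section 2.2, exclusion criterion 1 removes patients with "current unemployment or reduced earning capacity pension with no immediate prospect of employment".

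**The concern.** Two things do not fit. First, the three figures in one sentence (360, 16%, 320) are inconsistent with each other, and the randomised total of 400 is built on the last of them. A reader cannot tell whether 16% or 320 was intended.

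Second, a sample-size credit for explained variance is earned only if the covariates that explain the variance are in the analysis. One of the three named sources is missing from the stated model. A second is dated at application in section 2.7 and at admission in section 2.9, and exclusion criterion 1 may narrow its spread.

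At stake is how the result is read. A null finding would be judged against a claim of 80% power that the model in section 2.9, as described, does not secure by itself.

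**Working it through.** **Inputs (all from section 2.7).** Control rate p1 = 0.51; odds ratio 2.0; allocation 3:1; two-sided alpha 0.05 (z = 1.960); power 0.80 (z = 0.8416); correlation 0.4; dropout 20%.

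**Step 1: the plan's 360.**
- Intervention rate p2 = 2 × 0.51 / (0.49 + 2 × 0.51) = 1.02/1.51 = 0.6755; difference 0.1655.
- Pooled rate = 0.25 × 0.51 + 0.75 × 0.6755 = 0.634.
- Control-arm n = [1.960 × √(0.634 × 0.366 × 4/3) + 0.8416 × √(0.51 × 0.49 + 0.6755 × 0.3245/3)]² / 0.1655² = (1.090 + 0.478)² / 0.0274 = 89.8, so 90.
- Total = 4 × 90 = **360**. This reproduces. A Wald calculation on the log odds ratio gives 360.9, and a standard logistic-regression formula with a binary covariate gives 359.3.

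**Step 2: the covariate reduction.**
- 0.4² = 0.16, and 360 × (1 − 0.16) = **302.4**, so 303 (304 for an exact 3:1 split). This does not reproduce 320.
- The cut actually taken is 1 − 320/360 = 11.1%, which corresponds to a correlation of √0.111 = 0.33.
- For a 16% cut to end at 320, the start would have to be 320/0.84 = 381.

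**Step 3: dropout.** 320/0.80 = **400**. This reproduces, so step 2 is the only step that fails. For comparison, 303/0.80 gives 379 randomised, and 360/0.80 with no covariate credit gives 450.

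**Step 4: power at 320 evaluable (240:80).** I use the plan's own rule, in which covariates explaining a share R² of the variance act like a sample of 320/(1 − R²). With n the effective control-arm size, power = Φ{[0.1655 × √n − 1.090] / 0.568}, where 0.568 = √(0.51 × 0.49 + 0.6755 × 0.3245/3).

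| R² from modelled covariates | Effective total | Effective control n | Power |
|---|---|---|---|
| 0 | 320 | 80.0 | 75.4% |
| 0.05 | 336.8 | 84.2 | 77.5% |
| 0.08 | 347.8 | 87.0 | 78.7% |
| 0.111 | 360 | 90.0 | 80.1% |
| 0.16 | 381 | 95.2 | 82.2% |

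**Step 5: indicators credited against terms modelled.**

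| Indicator credited in 2.7 | In the primary model of 2.9? |
|---|---|
| Incapacity of three months or more | Yes |
| Unemployment at application | Yes, but at admission; variation possibly limited by exclusion criterion 1 |
| Limited performance in last occupation | Not listed |

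The article does not split the correlation of 0.4 among the three indicators, so the loss from the missing one cannot be computed. Only the 75% to 82% range can be given.

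**The case against.** The strongest reply is that the slip does no harm. The correct subtraction would have asked for fewer patients, so under the plan's own correlation of 0.4 the trial has about 82% power. This stands: a reader might infer that the arithmetic error costs power, and it does not.

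The reply can go further. Two of the three indicators are in the model, together with site and SIBAR. SIBAR's social-medical index measures the risk of early retirement (section 2.6.2), so it may carry prognostic information of its own. Only about 11% explained variance is needed, and nothing in the article shows that the listed terms fall short. This also stands. It would be wrong to say that the credited covariates are mostly missing, or that only one of them can contribute.

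Nor do the documents show that unemployment is nearly constant. Exclusion criterion 1 appears to leave room for unemployed patients who have a job in prospect, and no unemployment rate is given. Restricted variation is plausible but not established.

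Finally, the odds ratio of 2.0 was set below the cited 2.41 and 3.49. At 2.41, with the same 51% control rate and no covariate gain, 320 evaluable would give about 91% power (Wald). That limits the practical risk. It does not correct the printed step or the mismatch between the two sections.

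**Conclusion.** The step from 360 to 320 is wrong as written: 16% gives about 303, and 320 is an 11% cut. The error is conservative under the stated correlation of 0.4. Separately, the 80% claim holds only if the covariates actually modelled explain at least about 11% of the variance. Power at 320 evaluable runs from about 75% with no gain to about 82% with the full 16%, and the article does not allow a closer figure.

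These figures assume an odds ratio of 2.0, a 51% control rate, 20% dropout, and the plan's variance-reduction rule. That rule comes from linear models and does not carry over directly to the log odds ratio in a logistic model. A reader might go on to infer power in the high sixties, on the view that 2.0 is a covariate-adjusted odds ratio. That needs an assumed covariate with the full 0.4 correlation in the model. It cannot be combined with the argument that the covariates are weak, because with weak covariates the adjusted and unadjusted odds ratios converge and power returns to about 75%. The documents do not support the lower figure.

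**What to change.** In section 2.7, keep the unadjusted 360, state that a 16% reduction gives about 303, and say that 320 evaluable (400 randomised) gives about 75% power with no covariate gain and about 82% with the full 16% gain, for an odds ratio of 2.0.

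Then reconcile sections 2.7 and 2.9:

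- Add the limited-performance assessment as a fixed effect if it is available in the routine data. Section 2.6.3 does not list it among the occupational data, so this has to be checked first.
- If it is not available, drop the covariate credit and quote about 75%.
- Use one time point for unemployment, either application or admission, in both sections.

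The change to section 2.7 is wording only, and no extra patients are needed. The one drawback is a quoted power that may be slightly less favourable than 80%.
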